#### (ii) Endpoints

***Primary endpoints***: *At one year follow-up *the principle outcome is modelled 10-year risk of cardiovascular events derived using the UKPDS risk engine [39]. The UKPDS model uses information on sex, ethnicity, smoking status, presence or absence of atrial fibrillation, systolic blood pressure, HbA_1c_, total cholesterol, and HDL-cholesterol to predict the 10-year risk of primary CVD. Predicted events are myocardial infarction, sudden cardiac death, other incident ischaemic heart disease, stroke, and peripheral vascular disease death. *At five-year follow-up*, the primary endpoint is a composite of cardiovascular mortality and morbidity (non-fatal myocardial infarction, non-fatal stroke, non-traumatic amputations and revascularisations). ***Secondary endpoints ***are all-cause mortality, development or progression of renal impairment, peripheral neuropathy, blindness, reduced visual acuity, macular oedema, retinopathy; health status, health utility, quality of life, anxiety, well-being, treatment satisfaction, health service costs (number of visits to general practitioners and hospital doctors for outpatient clinics, hospital admissions and prescribed medications). ***Intermediate endpoints ***are self-reported smoking status, diet, physical activity behaviour and medication adherence, HbA_1c_, total cholesterol, LDL-cholesterol, HDL-cholesterol, triglycerides, blood pressure, modelled 10-year cardiovascular risk (at five-year follow-up), self reported hypoglycaemic episodes, microalbuminuria, body mass index and plasma vitamin C.

### Measurement

Table 2 shows the distribution across time of measures relating to the screening procedure and the treatment phase of the study. Baseline measurements were carried out on all patients eligible for an OGTT following the screening phase of the study. These included the completion of questionnaires, physiological and anthropometric measures and venesection. Similar measurements are conducted at one year and five years after diagnosis, without repetition of the OGTT. The measurements at baseline, one-year and five-year follow-up are undertaken at outpatient clinical research facilities by trained staff following standard operational procedures and unaware of participants' study group allocation. Questionnaires are used to collect information on basic demographics, health behaviours, health utility, functional status and costs.

**Table 2 T2:** Measures used at baseline, one-and five-years in the *ADDITION-Cambridge*

Measures	**Baseline**			**1-year**			**5-year**		
	**C**	**RC**	**IT**	**C**	**RC**	**IT**	**C**	**RC**	**IT**
**Diabetes risk score calculation**	**X**	**X**	**X**						
**Questionnaires measures**									
1. Ethnic group, occupation, educational level and social class		**X**	**X**						
2 Smoking status, alcohol consumption		**X**	**X**		**X**	**X**	**X**	**X**	**X**
3. Rose angina questionnaire [51]		**X**	**X**				**X**		
4. Self-reported history of angina, heart attack and stroke		**X**	**X**		**X**	**X**	**X**	**X**	**X**
5. Medication adherence:									
All drugs during the last month [40]		**X**	**X**		**X**	**X**		**X**	**X**
Hypoglycaemic drugs during the last month [40]					**X**	**X**		**X**	**X**
6. EuroQoL EQ-5D [47] & SF-36 [45]/SF-8 [46]		**X**	**X**		**X**	**X**	**X**	**X**	**X**
7. Diabetes related quality of life: ADDQoL [44], Diabetes well-being: W-BQ 28 [44], Diabetes treatment satisfaction: DTSQ[44]					**X**	**X**		**X**	**X**
8. Spiegelberger Short form State Anxiety inventory [49]		**X**	**X**		**X**	**X**			
9. Consultation and relational empathy measure: CARE [48]		**X**	**X**		**X**	**X**			
10. Diabetes knowledge †					**X**	**X**			
11. EPAQ-2 [41]		**X**	**X**		**X**	**X**		**X**	**X**
12. IPAQ [42]		**X**	**X**		**X**	**X**	**X**	**X**	**X**
13. EPIC food frequency questionnaire [43]		**X**	**X**		**X**	**X**		**X**	**X**
14. Brief dietary questionnaire (adapted from the EPIC food frequency questionnaire) †							**X**	**X**	**X**
15. Costs comprising:									
Personal patient costs †		**X**	**X**						
Health Service and medication use previous 3 months (adapted from the Aberdeen Health Service Research Unit questionnaire) †					**X**	**X**	**X**	**X**	**X**
16. Neuropathy questionnaire (adapted from the Michigan Screening Instrument) †		**X**	**X**		**X**	**X**		**X**	**X**
**Biological measures**									
17. Waist circumference, height, weight, blood pressure, body fat impedance and ECG		**X**	**X**		**X**	**X**		**X**	**X**
18. Fasting capillary blood glucose		**X**	**X**						
19. Fasting, 30 and 120 min: venous whole blood glucose (OGTT), plasma glucose, plasma insulin.		**X**	**X**						
20. HbA_1c_, total cholesterol, HDL and LDL cholesterol, triglyceride, Vitamin C, Urinalysis, Urine albumin/creatinine ratio, Urea and Electrolytes, Creatinine, Albumin, Biliribin, Alanine Amino Transferanse (ALT), Alkaline Phosphatase, Aspartate Amino Transferase (AST), Thyroid Stimulating Hormone (TSH)		**X**	**X**		**X**	**X**		**X**	**X**
21. Modelled CVD risk calculated with the UKPDS risk engine [39]		**X**	**X**		**X**	**X**		**X**	**X**
22. Stereoscopic fundal photography								**X**	**X**
23. Mortality							**X**	**X**	**X**

†: Questionnaire developed for the study

#### Health behaviours

Smoking status, alcohol consumption, and medication adherence are assessed by questionnaire. Medication adherence is assessed by the Medication Adherence Report Schedule (MARS) questionnaire [40]. Physical activity is assessed using the EPAQ2 [41] and IPAQ [42] questionnaires. Dietary intake is evaluated using a validated food frequency questionnaire [43].

#### Health utility, functional status, quality of life, well-being, treatment satisfaction and anxiety

The generic and disease-specific instruments used are diabetes well-being questionnaire (W-BQ12) [44], SF-36 [45], SF-8 [46], Audit of Diabetes-Dependent Quality of Life (ADDQoL) [44], diabetes treatment satisfaction (DTS) [44], and EuroQol (EQ-5D) [47], consultation and relational empathy (CARE) measure [48] and the Spiegelberger Short form State Anxiety Inventory [49].

#### Costs

Personal patient costs to attend initial screening tests and health service use in the three months prior to follow-up are quantified using an adapted version of the Health Services Research Unit Aberdeen questionnaire that inquires about the use of services (consultations with healthcare professionals and hospitalisations) and medications [50].

Angina is assessed using the Rose angina questionnaire [51]. Neuropathy is evaluated using an adapted version of the Michigan Neuropathy Screening Instrument [52].

#### Physiological measures

Random and fasting capillary blood glucose concentrations were assessed by Hemocue (β-HemoCue AB, Angelholm, Sweden). The venous plasma blood glucose level is assessed by the glucose dehydrogenase method and read photochromatically. The stability of the analyser was checked daily and external calibration with the Hemocue quality assurance scheme was undertaken monthly. HbA_1c _was analysed in capillary blood samples from general practices using the Bio-Rad^® ^system and in venous samples at the time of diagnostic testing by ion-exchange high-performance liquid chromatography on a Tosoh machines (Tosoh Bioscience, Redditch, UK). Serum total cholesterol, HDL-cholesterol and triglycerides are measured by means of enzymatic techniques (Dade Behring Dimension analyser, Newark, USA). Plasma creatinine is analysed with kinetic colorimetric methods, urine albumin by rate nephelemetry (Dade Behring Nephelometer II, Newark, USA). Plasma levels of urea and electrolytes, bilirubin, alanine aminotansferase (ALT), aspartate aminotransferase (AST), alkaline phosphatase, and thyroid stimulating hormone (TSH) and urine levels of creatinine are assayed by means of the Dade Behring Dimension analyser. Plasma vitamin C level was measured with a Fluoroskan Ascent FL fluorometer. The albumin-to-creatinine ratio (ACR) is measured on a random spot urine specimen. For assays requiring fasting, participants attend after a 10-hour fast.

#### Anthropometry

Blood pressure is calculated as the mean of three measurements performed after at least 10 minutes rest, while participants are seated with the cuff on the predominant arm at the level of the heart, using an automatic sphygmomanometer (Omron M4, UK). ECG is recorded by a 12 lead machine. Body height and weight are measured in light indoor clothing and without shoes using a fixed rigid stadiometer and a scale (SECA, UK) respectively. Waist circumference is estimated as the average of two measurements taken with a tape measure halfway between the lowest point of the rib cage and the anterior superior iliac crests when standing. Body fat percentage is measured by bio-electrical impedance (TANITA, Tokyo, Japan).

#### Ascertainment of mortality and cardiovascular morbidity

Macrovascular and microvascular events in patients with screen-detected diabetes will be ascertained by a combination of strategies including electronic READ code searches of medical records for events, and notes extraction on potential cases of events. Anonymous case reports packs will be prepared by a member of the research team unaware of participants study group allocation for independent review of each potential event by an endpoint committee also unaware of study group allocation. All patients will also have an ophthalmologic evaluation including stereoscopic fundal photography at the five-year assessment. Fundal photography will be assessed by a separate endpoint committee blind to study groups. ICD-10 coded mortality data is reported periodically by the ONS for all high-risk participants in the three arms.

Assessment of the effect of screening in a random sample of people at high risk of prevalent undiagnosed diabetes in each of the three study groups (IT, RC and control) will be undertaken by postal questionnaire in 2009, six years on average post randomisation. This questionnaire includes demographic characteristics, self-reported history of angina, heart attack and stroke, self-reported smoking status, IPAQ, simple dietary behaviour questions, EuroQoL (EQ-5D), Short Form-8 (SF-8), and the adapted version of the Health Services Research Unit Aberdeen questionnaire for the use of medication and services.

### Costs of the intervention

The economic analysis will establish the NHS costs of the initial screening programme for type 2 diabetes from a patient and health service perspective. We will examine the cost-effectiveness of the multifactorial intensive treatment of patients with screen-detected type 2 diabetes from a health service perspective.

### Participant retention

The retention rate at one year follow-up was 85%. In order to maximise retention, we are reimbursing patients' travel at follow-up assessment. We have also been sending annual Christmas cards to all participants. A few months before the start of the five-year assessment, we will send a newsletter to all participants outlining the one-year results and plans for inviting them back for re-measurement.

### Participant safety

Screening equipment was enrolled in the HemoCue quality assurance programme. The glucose tolerance test was undertaken by trained staff in dedicated testing centres. Treatment algorithms have been developed with advice from local diabetes specialists who also contributed to the initial and follow-up practice-based training sessions for primary care staff involved in diabetes care. The responsibility for prescribing and management decisions remains with the general practitioners. Classes of medication are only recommended within licensed indications.

In Cambridge, an independent Trial Steering Committee meets regularly and makes recommendations on ethical or safety aspects. At the European level, a Data Monitoring and Ethics Committee receives periodic reports on deaths and hypoglycaemic episodes. Termination of the study would be determined on the basis of mortality. Based on general trials stopping rules, it was suggested that the first interim analysis blind to study group (using data from the three countries) be undertaken when the total number of deaths reaches 200. The rule for termination is a significant difference in mortality between the IT and RC groups at a level of significance of 0.001.

## Statistical procedures

### Analysis

#### (i) Effect of intensive multi-factorial treatment

Analysis will be by intention-to-treat allowing for clustering of patients by practice. This will be supported by sensitivity analyses, assuming a range of outcomes for non-completers informed by baseline data. The main analyses will compare outcomes between patients with screen-detected diabetes receiving routine care (RC) and those receiving intensive treatment (IT), adjusting for differences in baseline variables. The primary perspective for cost analysis will be the health service.

At one year comparisons will be made on modelled 10-year cardiovascular disease (CVD) risk [39] and on secondary outcomes including individual cardiovascular risk factors, health utility, functional health status, and costs. The costs of the intensive intervention will then be compared with unit change in health utility. At five-years, analyses will include comparisons of main outcomes (fatal and non-fatal macrovascular events) and secondary outcomes (microvascular events, individual cardiovascular risk factors, all-cause mortality, health utility, functional health status, and costs).

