### ADDITION-Cambridge Objectives

The primary objective of the *ADDITION-Cambridge *study is to evaluate the effectiveness and cost-effectiveness of a stepwise screening programme for type 2 diabetes and intensive multifactorial treatment in people with screen-detected diabetes in English general practice.

The following research questions are posed:

• *Feasibility of screening*: What uptake and yield are achievable in a primary care-based stepwise screening programme for type 2 diabetes?

• *Costs of screening*: What are the health service and patient costs of screening for type 2 diabetes?

• *Early treatment of type 2 diabetes*: Can an optimised intensive intervention targeting blood glucose and associated cardiovascular risk factors reduce cardiovascular risk and mortality in people with screen-detected diabetes? Is this intervention cost-effective?

• *Population level impact: *Is a targeted screening programme for type 2 diabetes associated with reductions in population mortality and morbidity?

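### The one-year economic comparison uses change in health utility at a visit as its effect unit, so the result is not a cost per QALY and could be misread as one

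*Protocol article*

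**What the plan says.** Cost-effectiveness is part of the primary objective of the protocol article. Of the intensive treatment, the Objectives section asks: "Is this intervention cost-effective". The section on costs of the intervention repeats the aim: "We will examine the cost-effectiveness of the multifactorial intensive treatment of patients with screen-detected type 2 diabetes from a health service perspective". Neither place names an effect unit.

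The unit appears under Statistical procedures, Analysis (i). The text first fixes the viewpoint: "The primary perspective for cost analysis will be the health service". It then says that the one-year comparisons between arms cover modelled cardiovascular risk and "secondary outcomes including individual cardiovascular risk factors, health utility, functional health status, and costs". Next comes the sentence at issue: "The costs of the intensive intervention will then be compared with unit change in health utility". For five years the same paragraph lists health utility and costs among the outcomes to be compared and does not relate one to the other.

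Table 2 (item 6) schedules EQ-5D in both treatment arms at baseline, one year and five years, with nothing between baseline and one year. On resource use, the Costs paragraph under Measurement says that "health service use in the three months prior to follow-up are quantified". The article does not mention QALYs.

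**The concern.** Cost builds up over a period, whereas utility at one year is a reading on one day. Two arms can show the same one-year difference in utility after very different amounts of health gained during the year, and cost per unit change in utility cannot tell them apart.

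The question under study is one of policy: whether early intensive treatment is worth its cost. A reader will want to set the result beside other uses of health service money, which needs a common unit of health over time. The stated unit is on a 0 to 1 utility scale and looks like a QALY, so it invites that comparison without supporting it. Timing matters in this trial because Table 1 adds treatment in steps from baseline to 12 months, so a gain that builds gradually is plausible.

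Two further points in the same sentence are open. The cost of the intensive intervention may mean what it costs to deliver, or the difference in health service cost between arms. Nothing is said about the utility of a patient who dies before the one-year visit.

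**Working it through.** The article gives no cost, utility or cost-effectiveness result, so there is no figure of its own to reproduce. The check is on the unit.

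**Inputs.** The utility difference at one year is *d* = 0.05. This is the 5-point EuroQol difference in the Sample size section, taken as 0.05 on a 0 to 1 scale (assumption; the factors in the first four rows of the table do not depend on it). Baseline utility is taken as equal in the two arms. *C* is the cost set against the effect. *f* is the QALY gain over the year divided by *d*.

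**Formulas.** As written: *C*/*d*. Per QALY at the same cost: *C*/(*f d*). Cost per QALY divided by the as-written figure: 1/*f*.

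| Time path of the utility difference (assumed) | *f* | QALY gain | Cost per QALY ÷ as-written figure |
|---|---|---|---|
| Full gain at once, then held | 1.00 | 0.0500 | 1.0 |
| Linear to 6 months, then held | 0.75 | 0.0375 | 1.33 |
| Linear over the year | 0.50 | 0.0250 | 2.0 |
| None to 6 months, then linear to 12 | 0.25 | 0.0125 | 4.0 |
| Linear to 0.10 at 3 months, then falling linearly to 0.05 at 12 | 1.375 | 0.06875 | 0.73 |

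The last row is 0.5 × 0.25 × 0.10 + 0.75 × (0.10 + 0.05)/2 = 0.0125 + 0.05625 = 0.06875, and 0.05/0.06875 = 0.73.

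With an illustrative cost of 1,000 per patient and linear change, the as-written figure is 1,000/0.05 = 20,000 per unit of utility. The cost per QALY is 1,000/0.025 = 40,000.

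**Numerator.** If the between-arm difference in health service cost is *k* times the delivery cost, and the as-written figure uses delivery cost, the factor becomes *k*/*f*. With linear change (*f* = 0.5):

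- *k* = 0.5 gives 1.0
- *k* = 1 gives 2.0
- *k* = 1.5 gives 3.0
- *k* = 2 gives 4.0

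The ambiguity can therefore cancel the timing effect or double it.

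**Deaths.** Assume baseline utility 0.80, survivors at 0.85 (intensive) and 0.80 (routine) at one year, linear change, deaths at mid-year, and utility 0 afterwards. Mean QALYs in an arm with mortality *p* and survivor utility *u* are (1 − *p*)(0.80 + *u*)/2 + *p* × 0.5 × 0.80.

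- No deaths: 0.8250 − 0.8000 = 0.0250.
- 1% in both arms: 0.99 × 0.0250 = 0.0248.
- 1% intensive, 2% routine: 0.82075 − 0.79200 = 0.0288.
- 2% intensive, 1% routine: 0.81650 − 0.79600 = 0.0205.

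Equal mortality hardly matters. A one-point difference moves the gain by +0.0038 or −0.0045, about 15% to 18% of 0.0250.

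**The case against.** A journal article condenses its economic methods, and how QALYs are built, how deaths are scored and what enters total cost would normally sit in a fuller document. That stands for missing detail. It does not answer the point about the unit, because the article states the unit.

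The harm also depends on a reader treating the figure as a cost per QALY. The article promises no such figure and cites no threshold, and the wording sets costs against utility change without strictly defining a ratio. This is fair: the stated quantity is not wrong in itself by a factor of two. It is a poor unit for the question asked.

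The direction is not fixed either. Gains that start late or build up make the figure look too favourable, but an early gain that fades does the opposite, and the documents do not say which will occur.

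Three stronger readings are tempting, and the documents do not support them:

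- **That net cost is excluded.** The preceding sentence compares costs between arms, the viewpoint is the health service, and the Endpoints section counts visits, admissions and medication as health service costs. The between-arm difference is a natural reading; the wording is ambiguous.
- **That deaths are ignored.** The text is silent. Analysis is by intention to treat, with sensitivity analyses over assumed results for people who do not complete, and deaths could be scored there.
- **That this is the only cost-effectiveness measure planned.** The five-year list is introduced as what the analyses will include, and the section on costs of the intervention is not limited to the one-year comparison.

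**Conclusion.** The point holds for the effect unit. The article fixes the one-year unit as change in utility, a level at a visit, and a cost set against it is not a cost per QALY. Read as one at the same cost, it is half the true figure if utility changes linearly. Across the paths tried, the cost per QALY is between 0.73 and 4.0 times the as-written figure. With utility measured only at baseline and one year, the planned data cannot show which path applies, so the factor of two rests on the linear assumption.

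The cost numerator and the handling of deaths are ambiguities to settle in the same sentence, not demonstrated errors. The numerator can matter as much as the unit. Deaths matter little at one year unless mortality differs between arms. This is a cheap improvement to a stated method. The comparisons of clinical outcomes are unaffected.

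**What to change.** Replace the sentence with one to this effect: *One-year cost-effectiveness will be the difference (intensive minus routine) in mean health service cost, including the cost of the intervention, per QALY gained. QALYs will be the area under the EQ-5D utility curve from baseline to one year, with utility 0 from the date of death. The QALY difference will be adjusted for baseline utility, and the analysis will allow for clustering by practice.* If cost per unit change in utility is kept as well, say plainly that it is not a cost per QALY.

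The utility and mortality data for one year are already planned. Three costs should be named:

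- Linear interpolation between two visits is an assumption. Vary the time path in a sensitivity analysis, for example over the paths tabulated above.
- Service and medication use is recalled only for the three months before follow-up, so annual cost needs a stated extrapolation. Treatment steps run through the whole first year, so the last three months need not represent it.
- The result may look less favourable.

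An extension to five years should not be described as needing only data already collected, because the questionnaire does not record service use in the long gaps between its recall windows.

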#### (ii) Population effects of screening

People at high risk of having undiagnosed diabetes in the screening practices (IT and RC) will be compared to those in the no screening (control) practices to assess the impact of screening on mortality, cardiovascular morbidity, health status, self-reported diet, physical activity and health service costs using ONS and questionnaire data. This will be done using an intention to screen analysis. For the mortality analysis the primary outcome will be all-cause mortality and the secondary outcomes cardiovascular, cancer and other causes of mortality. Mortality, cardiovascular morbidity, health status, diet, and physical activity among people at high risk of having undiagnosed diabetes will also be compared between IT and RC groups in an intention to treat analysis to quantify the potential wider benefits of the practice-based intensive treatment intervention package.

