**Methods and design:**

The *ADDITION-Cambridge *study aims to evaluate the effectiveness and cost-effectiveness of (i) a stepwise screening strategy for type 2 diabetes; and (ii) intensive multifactorial treatment for people with screen-detected diabetes in primary care. 63 practices in the East Anglia region participated. Three undertook the pilot study, 33 were allocated to three groups: no screening (control), screening followed by intensive treatment (IT) and screening plus routine care (RC) in an unbalanced (1:3:3) randomisation. The remaining 27 practices were randomly allocated to IT and RC. A risk score incorporating routine practice data was used to identify people aged 40–69 years at high-risk of undiagnosed diabetes. In the screening practices, high-risk individuals were invited to take part in a stepwise screening programme. In the IT group, diabetes treatment is optimised through guidelines, target-led multifactorial treatment, audit, feedback, and academic detailing for practice teams, alongside provision of educational materials for newly diagnosed participants. Primary endpoints are modelled cardiovascular risk at one year, and cardiovascular mortality and morbidity at five years after diagnosis of diabetes. Secondary endpoints include all-cause mortality, development of renal and visual impairment, peripheral neuropathy, health service costs, self-reported quality of life, functional status and health utility. Impact of the screening programme at the population level is also assessed through measures of mortality, cardiovascular morbidity, health status and health service use among high-risk individuals.

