### Practice randomisation

Randomisation of practices was completed centrally and independently of the trial co-ordination team immediately following recruitment. The project statistician used a partial minimisation procedure that dynamically adjusted the randomisation probabilities to balance important baseline practice variables: the number of patients with known diabetes (<160 and ≥ 160 patients) and the local district hospital (Addenbrooke's, Hinchingbrooke, Peterborough, Kings Lynn, Broomfield, Stevenage and Bury St Edmunds hospitals). The first 33 practices recruited were allocated in a ratio of 1:3:3 to the following arms: control (no screening), screening followed by intensive multi-factorial treatment of diabetes (IT), and screening plus routine care of diabetes according to national guidelines (RC). Allocation of practices to the control (no screening) group was stopped at N = 5. The need to increase the yield of individuals with diabetes for the treatment trial warranted the uneven randomisation ratio with a disproportionate number of screening practices and a second stage of randomisation. 27 practices were subsequently randomised in a ratio of 1:1 to IT (n = 13) and RC (n = 14). The final group allocation after the two stages of randomisation included 28 practices to IT, 27 practices to RC and 5 practices to control (no screening). Six of the 60 randomised practices (2 IT and 4 RC) dropped out following recruitment, but before screening commenced due to other commitments or unforeseen difficulties in setting up the practice-based screening programme.

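### The screening-versus-control comparison pools 27 practices that could not have been allocated to control, so about half of the screening side lacks the protection of randomisation

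*Protocol article*

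**What the plan says.** All references are to the protocol article.

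- **Practice randomisation, first stage.** "The first 33 practices recruited were allocated in a ratio of 1:3:3 to the following arms": control, IT and RC. "Allocation of practices to the control (no screening) group was stopped at N = 5".
- **Practice randomisation, second stage.** "27 practices were subsequently randomised in a ratio of 1:1 to IT (n = 13) and RC (n = 14"). The abstract agrees: "The remaining 27 practices were randomly allocated to IT and RC".
- **Practice randomisation, drop-outs.** "Six of the 60 randomised practices (2 IT and 4 RC) dropped out following recruitment, but before screening commenced". The stage of these six is not given.
- **Timing.** "Randomisation of practices was completed centrally and independently of the trial co-ordination team immediately following recruitment". Practice recruitment gives September 2001 to August 2003 as the period in which practices were invited.
- **Analysis (ii), Population effects of screening.** High-risk people "in the screening practices (IT and RC) will be compared to those in the no screening (control) practices", on an intention-to-screen basis, with all-cause mortality as the primary outcome of the mortality analysis. The comparison is not limited to the first stage.
- **Design.** The population-level evaluation is presented as resting on the random allocation of practices to a no-screening group.

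**The concern.** A practice belongs to the randomised comparison with control only if it could have been a control practice. The 27 second-stage practices could not. They were randomised between IT and RC, but with respect to control they are simply practices that joined later and were all screened.

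The analysis section nevertheless names every IT and RC practice as the comparison group. Any systematic difference between earlier and later practices, such as in entry date or local mortality, then passes into the estimated effect of screening. The article itself, under the lack of trial evidence, warns that screening evaluations without random allocation are prone to selection and other biases and calls randomised evidence important for policy. The 5 control practices exist to supply that evidence.

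**Working it through.** **1. Reproduce the allocation.** Final allocation: 28 IT, 27 RC, 5 control, total 60. Second stage: 13 IT, 14 RC, total 27. First stage by subtraction:

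- IT: 28 − 13 = 15
- RC: 27 − 14 = 13
- Control: 5
- Total: 15 + 13 + 5 = 33, as stated.

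At 1:3:3 the expected number of controls among 33 is 33/7 = 4.7, so 5 fits. The article's counts are consistent.

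**2. Share of the screening side with no chance of being control.**

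- As randomised: 27/55 = 49%.
- After drop-outs: 55 − 6 = 49 screening practices. If all six drop-outs were second-stage, 21/49 = 43%. If none were, 27/49 = 55%.

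These are shares of practices. The article does not split the 35,297 high-risk people in screening practices by stage.

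**3. What pooling buys.** The second stage has no control practices. If the model includes a term for stage, those practices contribute essentially nothing to the screening effect. Any precision gained by pooling therefore comes from assuming that the two stages are exchangeable.

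**4. Size of a possible shift (illustration).** Shift in the pooled rate ratio ≈ second-stage share × relative difference in mortality between stages. The article gives no stage-specific rates, so the 5% and 10% are assumptions.

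| Stage difference | Share 21/49 | Share 27/49 |
|---|---|---|
| 5% | 2.1% | 2.8% |
| 10% | 4.3% | 5.5% |

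**5. Against a small population effect (illustration).** Enrolled cases are y = 867/35,297 = 2.46% of the high-risk screening population. Assume that cases have r = 1.5 to 2.5 times the mortality of other high-risk people. Apply the 26–40% reductions that the article quotes from modelling, and assume no effect in anyone else. The fall in all-cause mortality is y·r / [1 + y(r − 1)] × reduction:

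- Low end: 0.0246 × 1.5 / 1.0123 × 0.26 = 0.9%
- High end: 0.0246 × 2.5 / 1.0368 × 0.40 = 2.4%

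The 5% scenario (2.1–2.8%) overlaps this range; the 10% scenario (4.3–5.5%) lies above it.

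**6. Against sampling error (illustration).** Control high-risk population: 39,434 − 35,297 = 4,137. If 4–10% of them die (an assumption), there are 165 to 414 control deaths. The standard error of the log rate ratio from controls alone is 1/√414 to 1/√165, or 4.9–7.8%, before clustering. A 2.1–2.8% shift is then about 0.3 to 0.6 standard errors at most.

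**7. Cost of restricting to the first stage.** With equal practice sizes and variances, the standard error is proportional to √(1/5 + 1/k) for k screening practices. The first stage keeps 28 − 6 = 22 to 28. Relative to k = 49:

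- k = 28: √[(1/5 + 1/28)/(1/5 + 1/49)] = 1.034
- k = 22: √[(1/5 + 1/22)/(1/5 + 1/49)] = 1.055

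The 5 control practices dominate the variance, so losing the second stage costs little.

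**The case against.** **Stage may be handled in an analysis plan that is not shown.** The analysis section is a short passage with no model or covariates, and silence on these is no fault in a journal article. This stands for the modelling detail. It does not remove the point, because the article does state which practices are compared, and that set includes practices that could not have been control.

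**The stages may hardly differ.** All practices were invited within about two years. Deaths are captured in every arm through the same national tagging, and one postal questionnaire in 2009 serves all arms. The article does not show that the second-stage practices differed in area or patient mix. This stands: the bias may be small, and with 5 control practices it may lie below sampling error.

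**Restriction is not a perfect remedy.** Five control practices cannot cover seven district hospitals, so full adjustment for the minimisation factors is out of reach whichever set is used. All six drop-outs were screening practices. If all were first-stage, 6/28 = 21% of that group was lost after randomisation. The article also does not say whether control closed exactly at the 33rd practice. These are limits of the data and give no reason to prefer the pooled set.

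**Stronger readings that a reader might infer, and that the documents do not support:**

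- *The whole screening comparison is observational.* The first-stage contrast, 28 against 5 as allocated, was randomised.
- *The intention-to-screen label is wrong.* That term concerns analysing everyone eligible whether or not they attended. It fits either set of practices.
- *The bias exceeds any real effect.* The illustrative ranges overlap, the stage differences are assumed, and the effect calculation ignores the wider benefit among high-risk people that the article considers possible.
- *The treatment trial is affected.* Both stages randomised practices between IT and RC.

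**Conclusion.** The point holds as a should-fix. The stated comparison of screening with no screening includes 27 of 55 screening practices as randomised (43–55% of the 49 remaining) that were never randomised against control. The Design section nevertheless bases this evaluation on random allocation. The counts follow directly from the article.

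The size of any bias is unknown. The illustrative shifts in the rate ratio rest on assumed stage differences and on shares by practice rather than by person. They are similar to or larger than a small population-level effect, and possibly below sampling error. Non-concurrence concerns entry dates only, and the invitation window bounds it at about two years. The point does not rank higher because the stated primary endpoints belong to IT versus RC, which is unaffected.

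**What to change.** - Make the primary population-effect comparison the 5 control practices against the IT and RC practices randomised in the first (1:3:3) stage of 33. Confirm from the randomisation records that control was still open for each.
- Allow for clustering by practice. Adjust for the minimisation factors only as far as 5 control clusters permit.
- Report the comparison with all screening practices as a labelled sensitivity analysis that assumes the two stages are exchangeable.
- State the stage of the six practices that dropped out.
- Keep both stages for IT versus RC.

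The change is to analysis wording and needs no new data. The standard error of the screening contrast rises by about 3–6%, before any covariate adjustment.
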